## Assignment of interventions: blinding

### Who will be blinded {17a}

The study participants are not blinded. JRS is not blinded, but JRS attempts to minimize the potential influence by (a) assigning participants at the end of the inclusion visit, so that questionnaires and ratings at T0 are before the allocation. (b) JRS did not routinely check the participants’ group during the intervention.

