### Who will take informed consent? {26a}

JRS contacts the relatives by phone and informs them about the study. If they wish to participate, JRS sends written information about the R-bipolar study. At the following inclusion interview, an informed consent is signed by both the participant and the investigator conducting the interview. This investigator will primarily be JRS, but in case of high work-load or sickness absence, other members of the research group, who are trained in the relevant clinically rated observer-based scores (HAM, YMRS, and FAST) will perform the inclusions, including obtaining informed consent.

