**Fig. 1 Fig1:**
[figure not shown]
Spirit study schedule of enrolment, interventions, and assessments

*Primary outcome*: Daily self-reported mood instability collected via the Monsenso app^1^ [43] for relatives during the period in which the participants are part of the research project.*Secondary outcomes*: Other critically daily self-reported smartphone-based data including daily activity level, anxiety, irritability, stress, cognition, sleep, alcohol consumption, caregiver burden, and medicine as reported in [44].

Clinically rated observer-based scores on the following three scales: Hamilton Depression Scale-6 items (HAM-D6) [45] (being more sensitive in RCTs than the HAM-D17 [46]), the Young Mania Rating Scale (YMRS) [47] and the Functional Assessment Short Test (FAST) (a 24-item interviewer-administered interview concerning autonomy, occupational functioning, cognitive functioning, financial issues, interpersonal relationships and leisure time) [48].

Self-assessed scores on the following questionnaires: Burden Assessment Scale [49], Perceived Criticism Measure [22, 50], Carer Quality of Life [51, 52], Carer-Self-Efficacy [34, 53], Bipolar Knowledge Scale [54], Short Form-12 [55, 56], Brief Symptom Inventory [57], Perceived Stress Scale [58], Mood Disorder Questionnaire [59], Major Depression Inventory [60, 61], Childhood Trauma Questionnaire (CTQ) [62]. When the questionnaires are repeated after the intervention, the.

participants are asked to complete a satisfaction survey on the psychoeducation. The satisfaction survey was developed in close collaboration with the clinicians from the Copenhagen Affective Disorder Clinic.

*Tertiary outcomes*: Automatically smartphone-generated data on physical [63], and social activity [64].

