#### Mood instability—a sensitive primary outcome measure in randomized controlled trials

We have selected mood instability as the primary outcome measure in the RCT as this has several advantages: mood instability has internal validity as a real-life measure for patients and high external validity as it reflects patients’ illness severity and functioning. Extensive evidence shows that mood stability is of core pathogenetic significance in BD [67, 70–73]. Thus, a substantial proportion of patients with BD and relatives experience subsyndromal daily mood swings that are associated with increased perceived stress, decreased quality of life and functioning [67, 73], and increased risk of relapse and hospitalization for patients [70–72]. Increased mood instability behaves as a genetic vulnerability trait for BD as it is present in remitted patients [73] and their unaffected relatives [67]. Accordingly, during the last decade, there has been a gradual shift from a focus on affective episodes to inter-episodic mood instability [74, 75]. Mood instability is currently considered a new treatment target in BD as it appears to be a more sensitive measure of outcome in RCTs than more conventional outcomes focusing on relapse or recurrence of affective episodes [74–76].

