### Implementation {16c}

JRS and MFJ generated the randomization plan. JRS enrolled the participants and assigned participants to intervention or control groups at the end of each inclusion visit.

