### Data management {19}

The researcher, primarily JRS, collects sociodemographic data, clinical data, and outcome measures (besides the primary) including questionnaires electronically and easily via the RedCap database. The RedCap database is a secure web application for building and managing databases and online surveys and is approved for use in research projects by the Capital Region of Denmark. A logbook with contact information, information on related patients, participant ID number, and inclusion status is kept in an Excel file on a logged drive. Also, a logbook used to check participants’ registration activity in the Monsenso app is kept in an Excel file on a logged drive. The researcher enters data directly into RedCap and the Logbook. Only registration forms and completed consent forms are handled in paper form and these are stored in a locked file cabinet.

When participants use the Monsenso app, the data is automatically available to the researchers on the Monsenso webpage (www.portal.monsenso.com), which requires a username and password. When the trial is completed, the researchers can retrieve data for the entire cohort of participants.

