### Confidentiality {27}

At inclusion, all participants are given an individual identification number, which is used to link information between the database in RedCap, the logbook, and Monsenso. Only researchers associated with the R-bipolar project are given access to the project in RedCap. The logbook is kept on a logged drive to which only research members of the R-Bipolar study in the Copenhagen Affective Disorder research Centre (CADIC) have access.

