#### Estimation of mood instability

Estimates of instability will be based on readings obtained via the Monsenso system. Relatives and patients score their daily mood on a 9-point scale (patients on a scale from − 3 to + 3 and relatives on a scale 0–8). For each participant, a mood instability measure will be estimated for each day and aggregated in accordance with prior definitions by applying the root mean square successive difference (rMSSD) method [78–80]. The daily mood instability measures, reflecting the extent to which a daily and the previous day’s scores of self-monitored mood differ from one another during follow-up, will be computed as the squared successive difference (SSD) of the reported values. Consequently, daily instability measures can only be computed when consecutive daily values are present. The resulting SSD values are aggregated for each participant as the root mean square successive difference (rMSSD), taking the square root of the mean of the SSD values [80–83]. The instability measures will be computed following the original definition of the rMSSD score. The differences are squared such that positive and negative differences do not cancel out when the values are aggregated by computing the mean. Squaring the values also puts more weight on larger differences. Finally, the square root of the mean puts the aggregated value back on the original scale.

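### The primary outcome has no pre-randomisation value and the stated primary model uses no baseline information, which costs precision but does not bias the comparison

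*Protocol article*

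**What the plan says.** The protocol article fixes the order of events in several places.

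- **Consent {26a}:** "At the following inclusion interview, an informed consent is signed by both the participant and the investigator conducting the interview".
- **Allocation, Implementation {16c}:** the researcher "assigned participants to intervention or control groups at the end of each inclusion visit".
- **Blinding {17a}:** neither participants nor the assessing researcher are blinded. One stated safeguard is "assigning participants at the end of the inclusion visit, so that questionnaires and ratings at T0 are before the allocation".
- **Primary outcome, Outcomes {12}:** daily app-based mood instability, collected "for relatives during the period in which the participants are part of the research project".
- **Data handling:** the data entered in REDCap include "outcome measures (besides the primary) including questionnaires" (Data management {19}). The identifier that links REDCap, logbook and app is issued at the same point: "At inclusion, all participants are given an individual identification number" (Confidentiality {27}).
- **Computation, Estimation of mood instability:** "daily instability measures can only be computed when consecutive daily values are present". The squared differences are then combined into one rMSSD per participant.
- **Model, Statistical methods {20a}:** a two-level linear mixed model with a fixed effect of group and a random effect of person. No baseline or period term is named.

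No app run-in before allocation is described. The schedule is in Fig. 1, which is not shown in the text at hand.

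**The concern.** The timing of allocation is offered as a safeguard in an open trial, but it secures a starting value only for the questionnaires and ratings. The outcome on which the trial will be judged has none.

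This matters because people are likely to differ in mood instability before anything is done. The article itself says: "Increased mood instability behaves as a genetic vulnerability trait for BD". The sample also mixes types of relative, such as partners and parents, and the additional analyses {20b} treat relationship type as a possible effect modifier. If part of the spread in follow-up rMSSD is a lasting difference between people, a baseline value would remove that part from the error of the group contrast. It would also show whether the arms were alike at the start. With neither a baseline value nor another pre-allocation covariate in the model, precision is lost. An analysis plan could add covariates, but it could not create app data that were not collected before randomisation.

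**Working it through.** **1. Can a pre-allocation value exist?**

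- Consent: at the inclusion interview ({26a}).
- Allocation: at the end of the inclusion visit ({16c}, {17a}), which reads as the same occasion.
- Linked app data: from inclusion at the earliest ({27}), within the period of participation ({12}).
- Minimum for one squared successive difference: scores on 2 consecutive days.

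Even if the app were installed and a score entered during the visit, one day gives 0 successive differences. The number of pre-allocation rMSSD values is therefore 0. This step does not need Fig. 1. Only the statement that recording starts after allocation is inferred.

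**2. Does the stated model recover baseline information?**

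With one rMSSD per participant, a person random effect cannot be separated from residual error. If daily squared differences were modelled instead, all of them would still come after allocation. The person effect would then describe between-person spread without separating prior level from treatment effect. The model does not stand in for a baseline.

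**3. The plan's own sample size, used as a reference point.**

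Total N = 2 × 2 × ((1.96 + 0.84) / d)², with d the standardised difference and the number per arm rounded up.

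- d = 0.5: 63 per arm, 126 in total, the figure in Sample size {14}.
- A difference of 0.2 with SD 2.6: 2,653 per arm, 5,306 in total, which is not 126.
- Inflation: 126 × 1.3 × 1.1 = 180.2, which matches 180.

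The mismatch is a separate sample-size matter, and a baseline would not repair it. The SD of 2.6 comes from patients, whereas relatives are scored on a different 0-8 scale. The steps below therefore use SD units.

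**4. What would a baseline covariate be worth?**

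Adjusting for a covariate with correlation rho to the outcome multiplies the residual variance by (1 − rho²). The article gives no rho, so the values are assumptions. The standard error with 90 per arm (the planned 180) and outcome SD 1 is √(2/90) = 0.149 unadjusted. Clustering and dropout are ignored.

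| Assumed rho | Variance removed | SE of contrast (SD units) | Total N equivalent to 126 at d = 0.5 |
|---|---|---|---|
| 0 | 0% | 0.149 | 126 |
| 0.3 | 9% | 0.142 | 116 |
| 0.5 | 25% | 0.129 | 96 |
| 0.7 | 49% | 0.106 | 66 |

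For example, at rho = 0.5 the SE is 0.149 × √0.75 = 0.129. The number per arm is 2 × 0.75 × (2.80 / 0.5)², just over 47, rounded up to 48, so 96 in total.

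**5. Which row applies?**

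A run-in rMSSD is the same measure taken earlier and could plausibly reach the middle or lower rows. T0 stress, symptom and depression scores are different constructs, so a value nearer 0.3 is more realistic. Neither can be fixed from the article.

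**The case against.** **Validity.** A reader might infer that a chance imbalance could be mistaken for an effect, or that improvement cannot be tested without a starting value. The document does not support this. Randomisation makes the contrast unbiased in expectation, the standard error already allows for chance imbalance, and a parallel-group superiority test compares arms at follow-up. This objection stands in full.

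**Trait.** The article gives no test-retest figure, and the same section presents mood instability as a treatment target and a sensitive outcome. It does not establish that most of the variance is stable, so the gain can only be shown as a range.

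**Open recording.** It is tempting to add that arm-dependent reporting is the consequence. Lack of blinding is already listed as a limitation, and a run-in would not change reporting during follow-up. Retention {18b} also provides weekly app checks with phone or text contact.

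**Early app days.** Days between allocation and the first session could show early comparability. They come after open allocation, however, and the article defines no such window, so they are at most a sensitivity analysis.

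**Analysis plan.** Covariates are commonly left to the analysis plan, and the lack of a list in the article is not held against it here. What stands is that the design leaves no baseline for the primary measure, which no analysis plan can supply.

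**Timing.** By January 5th, 2024, 185 relatives had been included and recruitment was due to end that month. A run-in can hardly help this trial, and this objection stands.

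**Conclusion.** The point holds as a loss of precision. Under the described schedule no pre-randomisation rMSSD can be computed, and the stated model uses no other pre-allocation information. The group contrast therefore carries the full between-person variance, and comparability of the arms on the primary measure cannot be shown.

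The size depends on an unknown correlation: 9%, 25% or 49% of variance at assumed values of 0.3, 0.5 or 0.7. The gain still open to this trial, from T0 covariates, is probably near the lower end. The conclusion rests on reading the inclusion interview and the inclusion visit as one occasion, and on there being no undescribed run-in. It is not a finding of bias. It also gives no power figure for this trial, because the SD comes from patients and the stated difference does not reproduce the stated sample size.

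**What to change.** 1. **Primary model (Statistical methods {20a}, or the analysis plan).** Name a small set of T0 measures taken before allocation as covariates, for example the Perceived Stress Scale, the Brief Symptom Inventory and the HAM-D6. Fix the set before group codes are seen, which fits the blinded analysis promised in {17b}. The cost is a sentence of analysis wording, since the data are already collected. This is the change that applies to the present trial.
2. **Limitations (Discussion).** Only the lack of blinding and of long-term follow-up are listed. Add that the primary outcome has no pre-randomisation value, so comparability on it cannot be checked. This costs nothing.
3. **Any relatives still to be enrolled, or a successor trial.** Keep consent, T0 ratings and app set-up at the inclusion visit. Collect 7-14 days of app scores, then allocate and give the result by the phone or text contact already in use. Take the run-in rMSSD as the baseline covariate. The cost is a short delay. Courses run three times a year, so many relatives would be waiting anyway, but late inclusions may move to the next course.

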### Procedure for unblinding if needed {17b}

Statistical analyses will be carried out blinded for randomization status (intervention versus control) until the results are clearly described.

## Data collection and management

### Plans for assessment and collection of outcomes {18a}

JRS will assess all participating relatives, unless sickness or an extraordinary busy period, requires assistance from a colleague. JRS has prior experience with the Hamilton rating and was trained in FAST and YMRS before the start of the trial. The questionnaires used are described in the outcome section {12}.

### Plans to promote participant retention and complete follow-up {18b}

We check weekly to see if the participants remember to record in the Monsenso App. If there is a lack of adherence, we contact participants by phone call or text message, whichever is most suitable in the case. JRS sends emails with a reminder and a link to the questionnaire in Redcap 1 to 2 weeks prior to follow-up interviews, thus increasing adherence. If a participant wishes to leave the study, the date and reason are noted in the primary logbook.

### Data management {19}

The researcher, primarily JRS, collects sociodemographic data, clinical data, and outcome measures (besides the primary) including questionnaires electronically and easily via the RedCap database. The RedCap database is a secure web application for building and managing databases and online surveys and is approved for use in research projects by the Capital Region of Denmark. A logbook with contact information, information on related patients, participant ID number, and inclusion status is kept in an Excel file on a logged drive. Also, a logbook used to check participants’ registration activity in the Monsenso app is kept in an Excel file on a logged drive. The researcher enters data directly into RedCap and the Logbook. Only registration forms and completed consent forms are handled in paper form and these are stored in a locked file cabinet.

When participants use the Monsenso app, the data is automatically available to the researchers on the Monsenso webpage (www.portal.monsenso.com), which requires a username and password. When the trial is completed, the researchers can retrieve data for the entire cohort of participants.

### Confidentiality {27}

At inclusion, all participants are given an individual identification number, which is used to link information between the database in RedCap, the logbook, and Monsenso. Only researchers associated with the R-bipolar project are given access to the project in RedCap. The logbook is kept on a logged drive to which only research members of the R-Bipolar study in the Copenhagen Affective Disorder research Centre (CADIC) have access.

### Plans for collection, laboratory evaluation, and storage of biological specimens for genetic or molecular analysis in this trial/future use {33}

N/A, biological specimens are not collected in this trial.

## Statistical methods

### Statistical methods for primary and secondary outcomes {20a}

#### Statistical analyses

Analyses will be conducted for the total sample of 200 relatives and their corresponding patients with BD. Two-level linear mixed-effect models will be used including a fixed effect of group (active group versus control) and a person-specific random effect allowing for individual variation in mood instability or other outcome measures.

In relation to hypothesis 3, it will be investigated whether mood instability in patients and relatives covary more than mood instability in patients and healthy control individuals (controls collected as part of the ongoing Bipolar Illness Onset (BIO) study in the Copenhagen Affective Disorder Clinic [77].

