### Eligibility criteria {10}

Inclusion criteria: relatives of patients with BD who are affiliated with the Copenhagen Affective Disorder Clinic. It is the patients who decide which relatives they would like to invite for psychoeducation.Exclusion criteria: Insufficient Danish language, or age under 18 years.

Data from *patients* with BD are collected from the A-bipolar trial, which is another RCT that is currently running in the Copenhagen Affective Disorder Clinic [42].

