### Sample size {14}

According to prior analyses [73] mood instability in patients with BD varies on a scale from close to 0 to 10 with an average of 4.1 (SD = 2.6). Our power calculation is based on the assumption that group-based psychoeducation will be associated with a minimum decrease of 0.2 in mood instability compared to the placebo arm; for a power of 80% and a type 1 error risk of 0.05, we need to randomize a total of 126 patients (www.sample-size.net). Also, we need to adjust for situations where one patient has two involved relatives, making them interdependent (estimated to be 30%), and consider expected dropout (estimated to be 10%, as in our prior study [68]) resulting in a total sample size of 180. We expect 200 relatives to agree in participating in the RCT.

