### Recruitment {15}

Patients at Copenhagen Affective Disorder Clinical are routinely informed about the possibility of psychoeducation for their relatives. If interested, the patients will hand in a registration form with the name and phone numbers of their relative(s). The clinic generally recommends that patients start in psychoeducational group therapy themselves before their relatives are enrolled in psychoeducation. This is however only a recommendation and not a rule. Relatives’ psychoeducation groups are offered once in the autumn and two during spring.

Data from patients with BD are collected from the A-bipolar study, which is a parallel ongoing study [42]. We will secure written consent from the participants in the A-bipolar study to utilize their data in the R-bipolar study.

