## Assignment of interventions: allocation

### Sequence generation {16a}

On the webpage www.randomization.com, we produced a randomization plan. The random numbers allocated the participants in either intervention (1) or control group (2).

We chose to have block randomization to achieve equal sizes of the groups during the ongoing recruitment process. If two participants were related to the same patient, they would be grouped together, as they would not be independent participants.

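### Patient outcomes can come only from consenting A-bipolar participants, yet the plan describes the patients of all 200 relatives and its model omits the A-bipolar arm

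*Protocol article*

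**What the plan says.** All references are to the protocol article.

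- **Analysis set.** Statistical analyses {20a}: "Analyses will be conducted for the total sample of 200 relatives and their corresponding patients with BD". No number of patients is given.
- **Model.** Same section: "Two-level linear mixed-effect models will be used including a fixed effect of group (active group versus control) and a person-specific random effect". No term for any other trial is named.
- **Source of patient data.** Eligibility criteria {10} says that patient data "are collected from the A-bipolar trial, which is another RCT that is currently running in the Copenhagen Affective Disorder Clinic". Recruitment {15} adds a consent step: "We will secure written consent from the participants in the A-bipolar study to utilize their data in the R-bipolar study".
- **Who may enter.** Eligibility criteria {10} admits "relatives of patients with BD who are affiliated with the Copenhagen Affective Disorder Clinic". The exclusions concern only language and age, and the patient need not be in A-bipolar.
- **Shared patients.** Sample size {14} estimates at 30% the situation in which a patient has two relatives in the study. Sequence generation {16a} deals with their allocation: "If two participants were related to the same patient, they would be grouped together, as they would not be independent participants".
- **Role of patient outcomes.** Under Hypotheses, mood stabilisation and other outcomes in patients form part of the secondary hypothesis.

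**The concern.** The analysis section reads as if each relative in the total sample brought a patient with outcome data. The eligibility and recruitment sections say something narrower. Patient outcomes exist only where the index patient is an A-bipolar participant and has agreed to reuse. A relative whose patient is outside A-bipolar, or does not consent, contributes nothing to the patient comparison. The patient results would then describe a subset, and a reader of the analysis section alone would take them for the full randomised sample.

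A second gap follows from the same source. Because A-bipolar is itself a randomised trial, each contributing patient carries a second allocation. The article fixes a model for patient outcomes without using it. In a subset of modest and unstated size, the two R-bipolar arms can differ by chance in their mix of A-bipolar arms. Any effect of A-bipolar would then add noise that a known variable could remove.

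**Working it through.** **Plan's own figure.** There is none to reproduce for patients. The article's sample size concerns the primary outcome in relatives. Its last step, from 126 to 180, is consistent with 126 × 1.3 × 1.1 = 180.2, but this says nothing about how many patients supply data.

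**Step 1: does the data source secure the stated set?**
- Relative eligible: the patient is affiliated with the clinic.
- Patient outcome available: the patient is in A-bipolar and consents.

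The first condition does not imply the second. Full overlap is possible, but nothing in the article guarantees it, and the share of index patients in A-bipolar is not given.

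**Step 2: patients behind 200 relatives if overlap were complete.** The article does not say whether the 30% is of patients or of relatives.
- If 30% of patients have two relatives, there are 1.3 relatives per patient. Patients = 200 / 1.3 = 153.8, about 154, of whom about 46 have two relatives.
- If 30% of relatives are in pairs, 60 relatives form 30 pairs and 140 are single. Patients = 140 + 30 = 170.

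**Step 3: what the patient comparison could detect.** Assumptions: two equal arms, two-sided 0.05, 80% power, unadjusted comparison of one value per patient, n patients per arm. Detectable standardised difference = (1.960 + 0.842) × √(2/n). The A-bipolar shares are assumed, because the article gives none.

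| Assumed share in A-bipolar | 154 patients: n per arm | Detectable | 170 patients: n per arm | Detectable |
|---|---|---|---|---|
| 100% | 76.9 | 0.45 | 85.0 | 0.43 |
| 75% | 57.7 | 0.52 | 63.8 | 0.50 |
| 50% | 38.5 | 0.64 | 42.5 | 0.61 |
| 25% | 19.2 | 0.90 | 21.2 | 0.86 |

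**Step 4: effect of omitting the A-bipolar arm.** The unadjusted R-bipolar difference contains an extra term: (difference between R-bipolar arms in the proportion on a given A-bipolar arm) × (A-bipolar effect on the outcome). R-bipolar allocation is random, so the first factor averages zero and there is no bias in expectation. In any one sample it is not zero, and the smaller the subset, the more it varies. The article gives neither the A-bipolar effect nor the size of the subset, so the term cannot be sized.

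**Step 5: conditional check on duplicated rows.** Suppose each patient's outcome were entered once per relative and the rows were treated as independent. With m rows per patient, variance inflation = Σm² / Σm.
- 154 patients: (107.7 × 1 + 46.2 × 4) / 200 = 1.46. Type I error = 2 × [1 − Φ(1.96 / √1.46)] = 0.105.
- 170 patients: (140 × 1 + 30 × 4) / 200 = 1.30. Type I error = 2 × [1 − Φ(1.96 / √1.30)] = 0.086.

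A simulation with 20,000 runs gave 0.108 and 0.088 with duplicated rows, and 0.052 in both cases with one row per patient.

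**The case against.** The best defence is that nothing is hidden. The article says where patient data come from and that consent will be sought. The figure of 200 is attached to relatives, and no number of patients is claimed. Exact analysis sets, covariates and observation windows are commonly left to the analysis plan. Random allocation in R-bipolar protects the comparison whether or not the A-bipolar arm is in the model, and only secondary patient outcomes are affected.

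Much of this stands. The source is disclosed, there is no systematic bias from the omitted arm, and the primary outcome is untouched. What does not fall away is that the article is not merely silent. It states an analysis set and a model, and neither fits the data source that it describes elsewhere.

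A reader might go further in four ways that the article does not support:

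- **Patients counted twice, with a 10.5% error rate.** No section says that patient outcomes are entered once per relative. For a patient outcome, the person in the person-specific effect is naturally the patient. Joint allocation of relatives also gives each patient one arm.
- **154 as the maximum number of patients.** The other reading of the 30% gives 170.
- **A-bipolar acts directly on these outcomes.** The article does not describe its intervention.
- **Patient days before the relative's allocation will be included.** The article does not say so, and the schedule figure is not available here.

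**Conclusion.** The point holds in limited form, for the patient part of the secondary hypothesis. The patient analyses are described through the total sample of relatives, while the data can come only from consenting A-bipolar participants, whose A-bipolar arm the stated model leaves out.

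The size is partly open. With full overlap there would be about 154 or 170 patients and a detectable standardised difference of 0.43–0.45. If half of the index patients were in A-bipolar, it would be 0.61–0.64, but that share is an assumption. The loss from omitting the A-bipolar arm is one of precision and chance balance, and it cannot be quantified from the article. The type I error of 0.086–0.105 is a conditional risk that one sentence on the unit of analysis would remove. It is not a feature of the stated plan.

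**What to change.** In Statistical methods {20a}, or in the analysis plan before analysis:

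1. Define the patient analysis set as index patients who are in A-bipolar and have consented to reuse, analysed as randomised through their relative or relatives. Do not call it the total sample.
2. Make the patient the unit: one patient-level random effect, with no duplication when a patient has two relatives.
3. Add the A-bipolar arm as a covariate in the models for patient outcomes.
4. Count patient outcomes from the relative's allocation date, over the same window as for relatives.
5. Report by R-bipolar arm how many patients contribute.

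The cost is some wording, one allocation variable from a sister trial run in the same clinic, and a smaller stated number for patient outcomes.
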